#### 12.4. Adjustment for covariates

For adjustment, age, sex, mini-mental state examination score, education, income, and baseline data of the outcome variable will be included in the ANCOVA model as covariates. Additionally, other variables that were found to be imbalanced between groups at baseline will also be included into the analysis.

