### 5.3. Randomization and blinding

Individuals who provide informed consent will undergo randomization through a 1:1 randomization sequence generated using Research Randomizer software (<https://www.randomizer.org/>). To ensure proper implementation, all aspects of the randomization process, including sequence generation and result disclosure, will be carried out by an independent researcher who will not be related to the study recruitment and outcome assessments. The randomization result will be disclosed only after the end of the baseline evaluation. Therefore, participants and outcome assessors will be blinded only in the baseline evaluation. Additionally, researchers responsible for performing statistical analysis will also be blinded. To ensure this, before extracting the data from the database, random codes for encoding the study groups will be generated by the same independent researcher responsible for allocation. The disclosure of group assignments will only occur after all analyses have been completed.

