### 12.1 Descriptive statistics and baseline data

A consolidated standards of reporting trials (CONSORT) style flow diagram will present the number of patients screened and all reasons for exclusions prior to randomization (9). Demographic and socioeconomic information (including age, sex, race, socioeconomic status, and educational level), baseline clinical characteristics (such as body mass index [BMI], glycated hemoglobin, systolic and diastolic blood pressure, insulin usage, smoking status, alcohol consumption, comorbidities, performance on up and go, gait speed, and sit and stand tests, and others), as well as other variables, will be described by arm and overall. Categorical variables will be described as frequency (percentage). Continuous variables will be described as mean  $\pm$  standard deviation (SD) or median and interquartile range. Hypothesis testing for differences in baseline characteristics between the intervention and control arms will not be performed, in accordance with the CONSORT guideline.

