### 12.2. Primary and secondary outcome analysis

All analysis will be performed after the end of the trial and no interim analysis will be performed. The analysis of all study outcomes will be carried out using analysis of covariance (ANCOVA), as all the outcomes are quantitative. This approach will allow a comparison of means between groups, while also considering potential variations in covariates. As we will compare the means at the end of the study, rather than deltas

(differences from baseline), the model will include baseline data of the outcome variable as a covariate. This adjustment allows us to account for the initial variation in scores among the groups before assessing any potential intervention effects.

All analysis will be performed using the intention-to-treat approach, including all subjects who were randomized. Per protocol analysis will only be performed as a sensitivity analysis, as described in the section 12.3. Normality tests for outcome data will not be performed. Instead, we will conduct visual histogram and QQ plot analyses. If distributional assumptions are in doubt, we will perform a logarithmic transformation of the data before analysis.

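### Section 12.4 lets unspecified baseline imbalance add covariates to the ANCOVA, so the primary SRQ-20 model is not fully pre-specified

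*Combined protocol and SAP*

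**What the plan says.** Section 12.4 opens with a fixed list: "For adjustment, age, sex, mini-mental state examination score, education, income, and baseline data of the outcome variable will be included in the ANCOVA model". Its next sentence opens that list: "other variables that were found to be imbalanced between groups at baseline will also be included into the analysis".

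Four other places bear on it:

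- **Section 12.2** applies ANCOVA to every outcome, so the open sentence covers the primary SRQ-20 comparison. The only covariate this section names is the outcome's own baseline value: "the model will include baseline data of the outcome variable as a covariate". On timing it says "All analysis will be performed after the end of the trial and no interim analysis will be performed".
- **Section 12.1** states "Hypothesis testing for differences in baseline characteristics between the intervention and control arms will not be performed". Its list of baseline characteristics is open-ended: "and others), as well as other variables, will be described by arm and overall".
- **Section 5.3** states that "researchers responsible for performing statistical analysis will also be blinded", by means of random group codes that are broken only once the analyses are finished.
- **Sections 12.6 and 12.7** give a significance level to the primary outcome alone and treat every other outcome as hypothesis-generating.

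**The concern.** In a randomised trial, a baseline difference between arms is chance. Its size says nothing about whether the variable predicts SRQ-20, and prediction is what makes a covariate worth having. The sentence therefore selects covariates on the wrong property.

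It also selects them without a rule. The plan does not say how imbalance is measured, how much is too much, which variables are eligible, who decides, or when. The customary (if poor) criterion would be a baseline significance test. Section 12.1 removes that for good reason, and section 12.4 supplies no other.

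Two analysts following the plan faithfully could therefore fit different primary models to the same data. Because all analysis comes after the trial ends and no step locks the covariates beforehand, the choice could be made with the SRQ-20 results in view. At stake is the error rate of the only test on which the trial will claim significance.

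**Working it through.** **1. The plan's own figure.** Section 11 gives alpha 0.05, power 90%, d = 0.68 and 47 per group. A two-sided two-sample t-test (noncentral t) has power 0.8973 at 46 per group and 0.9035 at 47, so 47 is reproduced. The calculation uses no covariates, so fixing the covariate list leaves it unchanged.

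**2. How many variables would be added by chance.** The input is 56 per arm (section 11). The number of candidates is not stated. Sections 9.1 and 12.1 name about 30 baseline measures beyond the fixed list, some overlapping (such as weight and BMI), so 10 to 20 is assumed.

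Under randomisation, the standard error of a standardised mean difference (SMD) is √(2/56) = 0.189. For a cut-off c, the chance per variable is 2[1 − Φ(c/0.189)]. For c = 0.2 this is 2[1 − Φ(1.058)] = 0.290. A p<0.05 criterion corresponds to an absolute SMD of about 1.96 × 0.189 = 0.37.

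| Cut-off on absolute SMD | Chance per variable | Expected additions, 10 candidates | Expected additions, 20 candidates | Chance of at least one, 10 to 20 candidates |
|---|---|---|---|---|
| above 0.10 | 0.597 | 6.0 | 11.9 | 1.00 |
| above 0.20 | 0.290 | 2.9 | 5.8 | 0.97 to 0.999 |
| above 0.25 | 0.186 | 1.9 | 3.7 | 0.87 to 0.98 |
| p<0.05 equivalent | 0.050 | 0.5 | 1.0 | 0.40 to 0.64 |

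The expected counts do not require independent variables; the last column does. With 20 candidates, the unstated cut-off alone moves the additions from about 1 to about 12, on top of the six fixed covariates.

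**3. Effect on type I error.** ANCOVA was simulated under no treatment effect with 47 per arm, six fixed covariates (the baseline outcome correlated 0.5 with the final outcome) and independent candidates. There were 8,000 replicates per row, with a Monte Carlo standard error of about 0.0024. The last column reports the smallest p-value of the five models.

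| Candidates, correlation with outcome | Fixed list | SMD >0.10 | SMD >0.20 | SMD >0.25 | p<0.05 | Best of five |
|---|---|---|---|---|---|---|
| 10, 0.10 | 0.049 | 0.048 | 0.044 | 0.043 | 0.048 | 0.076 |
| 10, 0.20 | 0.049 | 0.024 | 0.020 | 0.023 | 0.036 | 0.074 |
| 15, 0.15 | 0.052 | 0.030 | 0.029 | 0.030 | 0.041 | 0.086 |

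A separate simulation at 45 per arm with 10 to 20 candidates agreed: about 0.05 for the fixed list, 0.012 to 0.049 for a single cut-off, and 0.073 to 0.083 for the best of four.

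A single cut-off tends to be conservative because the variables left out are the well-balanced ones. They still add to the residual variance but contribute little to the error of the arm difference.

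**4. Effect on power.** With d = 0.68 and 10 candidates correlated 0.10 with the outcome (3,000 replicates), power was 0.953 for the fixed list and 0.949 to 0.953 for the four cut-offs. In that scenario the degrees of freedom spent on extra covariates cost almost nothing.

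**The case against.** The strongest defence is that little is left open. The endpoint, the time point, ANCOVA on final values, the intention-to-treat population, six covariates and alpha are all fixed. Imbalance at baseline can be judged without any week-12 value, and the analysts work on coded groups. All of this stands, and it limits the severity. It does not close the gap: no rule or lock is stated, and group codes make it hard to favour one arm but do not hide which model gives the smallest p-value.

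Four stronger readings are tempting, and the documents do not support them:

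- **That section 12.4 contradicts section 12.1.** Section 12.1 bars hypothesis tests only. Imbalance could be judged descriptively, for example by standardised differences, so both sections can be followed. The fault is an omission.
- **That the primary test is not pre-specified, or is driven by outcomes.** Only the additional covariates are open, and their trigger is a baseline feature.
- **That the sentence in itself inflates type I error.** Applied with any one cut-off, it did not do so in the simulations. Inflation appeared only when the best of several models was reported, and nothing in the plan proposes that. The plan merely fails to prevent it.
- **That the enlarged model would be fitted to about 90 people** (112 × 0.80 = 89.6). Section 12.2 includes everyone randomised, section 12.3 lists multiple imputation first, and completers are a sensitivity analysis. The primary analysis has the planned 112.

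**Conclusion.** The concern holds as a should-fix. The primary model is mostly but not fully specified: six covariates are fixed, and an unbounded set may join them on a criterion that is undefined and unrelated to prognosis.

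The cut-offs in the tables are illustrative, since the plan gives none, and the count of 20 candidates is an assumption. On those terms, between about 1 and about 12 covariates would be added. The error-rate results also rest on assumed independent candidates correlated 0.10 to 0.20 with the outcome in the tabulated runs. They show a test that is at or below its nominal level if one cut-off is applied mechanically (about 0.01 to 0.05), and above it if the cut-off is chosen after comparing results (about 0.07 to 0.09). A fixed list avoids both, at 0.049 to 0.052.

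The mismatch between section 12.2 (one covariate named) and section 12.4 (six and more) adds to the uncertainty about which model is primary.

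**What to change.** 1. Delete the second sentence of section 12.4.
2. State the same primary model in sections 12.2 and 12.4: week-12 outcome on arm, baseline outcome, age, sex, MMSE score, education and income, in all randomised subjects.
3. If adjustment for chance imbalance is wanted, add it as a labelled sensitivity analysis. Name the metric (for example the absolute SMD), one cut-off and a closed list of candidates, all fixed before outcome data are examined.

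Keeping the sentence and supplying a metric, cut-off, candidate list and lock date would also restore pre-specification. It would still select on imbalance rather than prognosis, and would often leave the test conservative.

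The cost is one sentence deleted, one aligned and one added, reported as a modification under section 17.4. The sample size and data collection do not change. The downside is that a strongly prognostic variable outside the fixed list that happens to be unbalanced would be adjusted for only in the sensitivity analysis.

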#### 12.5. Sensitivity and subgroup analysis

Sensitivity analysis will be conducted to assess the impact of missing data as described above. Also, pre-specified subgroup analysis will be performed: age (<80 vs.  $\geq 80$  years old), education level (graduate vs. undergraduate), sex (male vs. female), insulin usage (yes vs. no), history of depression (yes vs. no) and cognitive impairment (yes vs. no, accordingly to MMSE score adjusted for education level). Due to the increased risk of type I and type II error and reduced power, only subgroup analysis for primary outcome will be performed.

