### 5.1.2 Exclusion criteria

- Having an interactive virtual home assistance device at the time of enrollment;
- Having cognitive impairments or severe hearing impairments that prevent adequate interaction with outcome assessors and the application of follow-up questionnaires; or
- Residing in regions of difficult access.

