## 9.1. Data collected

**Identification data:** Full name, medical record number, phone number, address, and email address.

**Clinical interview and baseline evaluation:** Sociodemographic information, comorbidities and personal medical history, daily schedule, mini-mental state examination (MMSE) score,

up and go test, sit-to-stand test, usual gait speed test, height, hip and calf circumference, Katz activities of daily living index score, and Lawton instrumental activities of daily living scale

**Clinical evaluation:** Blood pressure (three repeated measures), handgrip strength (three repeated measures in the non-dominant arm), body weight, and score on the Brazilian version of the following:

- SRQ-20
- SF-36
- SCI-R
- PSS

**Laboratory evaluation:** Glycated hemoglobin, fasting plasma glucose, total cholesterol, HDL-c, LDL-c, triglycerides, serum creatinine, and albumin and creatinine (urine sample)

**Medication use:** Name and daily dosage of medications, vitamins and nutritional supplements, if in use

**Installation of the device:** During installation of the device no data is collected.

**Follow-up phone calls:** General information about well-being and adverse events

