### 12.3. Missing data

The imputation of missing data will be handled following the European Medicines Agency Guideline on Missing Data in Confirmatory Clinical Trials (10). The overall rate of missing data at week 12 is expected to be no more than 20% and the frequency and reasons for missing data are expected to be missing at random (MAR). However, the possibility of missing not at random (MNAR) cannot be excluded, as we believe that three factors may influence the missing data:

1. Participants less familiar with technology may have a higher tendency to dropout and might experience reduced benefits due to a higher likelihood of non-adherence to the intervention.

2. Participants from the usual care group may have a higher tendency to discontinue participation due to not receiving the device as they expected.

3. Older participants, who are less likely to experience intervention-related benefits, may be more likely to miss the final evaluation due to potential mobility challenges and a greater reliance on caregiver assistance to attend the consultation.

Therefore, to explore the potential impact of missing data in different scenarios, promoting a better understanding of how different methods of handling missing data impact our results considering the challenge of handling missing data within the possibility of MNAR assumption, three distinct imputation strategies will be employed to assess the impact of missing data on our results:

1. *Multiple imputation with baseline data correction*: we will perform multiple imputation of missing data correcting for the baseline data. This correction aims to mitigate potential bias that could be introduced by missing data imputation using multiple imputation under a possible MNAR assumption.

2. *Baseline Observation Carried Forward (BOCF)*: given our anticipation and belief that both control and intervention subjects are likely to exhibit improvement regarding the baseline parameters, we will adopt the BOCF technique as a sensitivity analysis. By carrying forward the baseline observation, our analysis will be conducted within a more conservative scenario that tends toward the null hypothesis, reducing the probability of type 1 error related to missing data imputation.

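### Effect modification by age is examined only as under 80 versus 80 and over; an arm × age-in-years term would use information that the split discards

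*Combined protocol and SAP*

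**What the plan says.** Section 12.5 states that "pre-specified subgroup analysis will be performed: age (<80 vs", with 80 years and over as the second group. Cognition is handled the same way, as "cognitive impairment (yes vs. no, accordingly to MMSE score adjusted for education level". Neither the choice of 80 nor the MMSE cut-offs are explained, no interaction test is named, and no arm-by-continuous-variable term is planned. The section recognises the limits of these analyses: "Due to the increased risk of type I and type II error and reduced power, only subgroup analysis for primary outcome will be performed".

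Both variables exist on a finer scale. Section 9.1 lists the "mini-mental state examination (MMSE) score" among the baseline data, and Section 5 has date of birth collected at records screening. Section 12.4 puts both in the model: "age, sex, mini-mental state examination score, education, income, and baseline data of the outcome variable will be included in the ANCOVA model as covariates". Those are main effects. They adjust the comparison but do not let the treatment effect vary with age or cognition, and the functional form for age is not stated.

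Section 12.3, in its account of why data may be missing, says: "Older participants, who are less likely to experience intervention-related benefits, may be more likely to miss the final evaluation".

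**The concern.** The plan names age as something that may reduce benefit and records it finely enough to study, yet examines it through one cut. If the effect falls steadily with age, people aged 66 and 79 are treated as alike, as are people aged 80 and 92. Most of the variation in age is then unused, in a trial sized for a single overall comparison. Entry starts at 65 with no upper limit, so the share aged 80 or over is unknown and could be small. At stake is how well the trial can describe whether older participants gain less. The primary result is not affected.

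**Working it through.** **Inputs from the documents.** Section 11: effect size 0.68 (Cohen's d), alpha 0.05, power 90%, 94 required (47 per group), 20% dropout, 112 planned. Section 5.1.1: age 65 or older. Section 4: 1:1 allocation.

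**The plan's own figure.** A two-sided two-sample t calculation with d = 0.68, alpha 0.05 and 90% power gives 46.4 per group, hence 47 per group and 94 in total. This reproduces Section 11. With 112 enrolled and 20% lost, 112 × 0.80 = 89.6, so about 90 are evaluable.

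**Assumption.** The documents give no age distribution. Let p be the share aged 80 or over; several distributions are tried.

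**Step 1: information kept by the split.** If the treatment effect changes linearly with age, the efficiency of the two-group analysis relative to a linear arm × age term is the squared correlation between age and the indicator of being 80 or over.

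- Normal age: φ(z)² / [p(1 − p)], where z is the normal quantile at 1 − p. At p = 0.10, 0.1755² / 0.09 = 0.34. At p = 0.20, 0.2800² / 0.16 = 0.49.
- Exponential tail above 65: (ln p)² × p / (1 − p). At p = 0.10, 5.302 × 0.10 / 0.90 = 0.59. At p = 0.20, 2.590 × 0.20 / 0.80 = 0.65.
- Normal truncated to 65–100: by simulation.

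Information lost (1 minus efficiency):

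| Share aged 80+ | Normal | Truncated normal | Exponential tail |
|---|---|---|---|
| 5% | 78% | – | 53% |
| 10% | 66% | 56–58% | 41% |
| 15–17% | 57% (at 15%) | 49% (at 17%) | 36% (at 15%) |
| 20% | 51% | – | 35% |
| 25–26% | 46% (at 25%) | 40% (at 26%) | 36% (at 25%) |
| 30% | 42% | – | 38% |

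The range is about 35% to 80%. The loss reaches one half only if p is at most about 21% (normal), roughly 16% (truncated normal), or near 5% (exponential tail).

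**Step 2: precision in the older stratum.** With n people split equally between arms, the SE of the mean difference in SD units is √(4/n), and the half-width is t × SE on n − 2 degrees of freedom.

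- p = 10%: n = 9, SE = 0.667, t = 2.365, half-width 1.58, about 1.6 SD.
- p = 20%: n = 18, SE = 0.471, t = 2.120, half-width 1.00 SD.

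These are unadjusted. If the stratum effects come from one model for all participants (t about 1.99) and baseline SRQ-20 correlates 0.5 with the outcome (an assumption; factor √(1 − 0.25) = 0.87), they become 0.667 × 1.99 × 0.87 = 1.15 SD and 0.471 × 1.99 × 0.87 = 0.82 SD. Both still exceed 0.68 SD.

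**Step 3: power for the interaction, linear case.** Suppose benefit falls by 0.068 SD per year, so that a mean effect of 0.68 SD is gone 10 years above the mean age. Simulation with 90 participants and baseline correlation 0.5 gives about:

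| Assumed age distribution | Share aged 80+ | Age in years | Split at 80 |
|---|---|---|---|
| Normal | 10% | 59% | 22% |
| Truncated normal | 8% | 41% | 16% |
| Truncated normal | 19% | 51% | 31% |
| Truncated normal | 26% | 58% | 37% |
| Exponential tail | 10% | 60% | 38% |

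The level depends on the spread of age: for this slope, power of the continuous analysis runs from about 39% at an age SD of 4.5 years to about 74% at 7 years. The continuous analysis is ahead in every row, by 20 to 37 percentage points.

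**Step 4: the opposite case.** Suppose the effect is 0.68 SD below 80 and zero from 80 on, with normal age. The split then has the higher power: about 20% against 10% at p = 10%, and about 32% against 18% at p = 20%.

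**The case against.** The strongest reply is that everything in Steps 1 and 3 assumes a roughly linear trend. A reader might infer from Section 12.3 that the investigators expect a gradient, with benefit falling year by year. The text does not say so. It says only that older participants are less likely to benefit, within an argument about missed visits, mobility and reliance on caregivers. That fits a contrast between the oldest and the rest equally well, and Step 4 shows that the split would then be the better analysis. A plot of some 90 people is a weak check between the two. This stands, and is why the split should be kept beside the continuous term. It does not justify using the split alone, since no threshold at 80 is argued anywhere.

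Second, these are secondary, pre-specified analyses of the primary outcome, reduced power is acknowledged, and Section 12.7 commits to 95% CIs for every subgroup. A reader might infer that a wide interval will be reported as no effect in the oldest participants; nothing in the plan says that. It also stands that the continuous analysis has only moderate power, so neither version would settle the question. But acknowledging scarce information is a reason not to discard more of it.

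Third, a reader might extend the same loss to cognition, or suppose the impaired group will be tiny because of the exclusion "Having cognitive impairments or severe hearing impairments that prevent adequate interaction with outcome assessors". That criterion removes only impairment that prevents assessment, so the remaining impaired group need not be small. Neither the MMSE cut-offs nor a distribution is given, so no loss can be calculated. Replacing the split by the raw score would also drop the education adjustment that Section 12.5 builds in.

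**Conclusion.** The point holds as an inexpensive improvement. Section 12.5 examines age modification only through a cut at 80, although age is already in the model and Section 12.3 expects older participants to benefit less. Under roughly linear modification, the cut loses about 35% to 80% of the information on the interaction. A reader might infer that at least half is always lost; the documents do not support that, because it depends on an age distribution they do not give, and the loss falls below half under several reasonable ones. The stratum half-widths of about 1.6 to 1.0 SD rest on about 90 evaluable participants, 10% to 20% aged 80 or over, and no covariate adjustment. For MMSE, the same structural remark applies but no size is claimed. The primary analysis is untouched.

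**What to change.** In Section 12.5, pre-specify an arm × age (years) interaction, added to the Section 12.4 ANCOVA for SRQ-20, as the main analysis of age modification. State in Section 12.4 that age enters in years. Report the change in treatment effect per 5 years and the fitted effect at ages 70 and 80, each with a 95% CI. Keep the under-80 versus 80-and-over estimates alongside, as a display and as a check on a threshold pattern, with the number of people per arm in each stratum.

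An arm × MMSE score term can be added in the same way as a secondary analysis, using an education-adjusted score or including arm × education in the same model.

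The cost is SAP wording: no new data and no change to the primary analysis. It should be written before group codes are disclosed; added later, it would be post hoc. The downside is the linearity assumption, which can be checked only weakly at this sample size, so the results should be labelled exploratory.
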